## Abstract

**Background:**

Hand osteoarthritis (OA) is one of the most prevalent musculoskeletal diseases in an adult population and may have a large influence on an individual’s functioning, health-related quality of life and participation in society. Several studies have demonstrated that exercises may reduce pain and improve functioning in people with knee OA, with a similar effect suggested for hip OA. For hand OA, available research is very limited and shows conflicting results, and high-quality randomised controlled trials are warranted.

This paper outlines the protocol for a randomised controlled trial that aims to determine the effect of an exercise intervention on self-reported hand activity performance in people with hand OA.

**Methods:**

Participants with physician-confirmed hand OA according to the ACR clinical criteria are being recruited from two Norwegian OA cohorts: the population-based “Musculoskeletal pain in Ullensaker Study” (MUST) OA cohort, and the hospital-based Oslo Hand OA cohort. Participants are randomised into an intervention- or control group. The control group receives “usual care”, whereas the intervention group receives a 12-week exercise intervention. The intervention group attends four group sessions and is instructed to perform the exercise program three times a week at home. Adherence will be captured using self-report. During the eight weeks with no group sessions, the intervention group receives a weekly telephone call. The assessments and group sessions are being conducted locally in Ullensaker Municipality and at Diakonhjemmet Hospital, Oslo. Outcomes are collected at baseline, and at 3 and 6 months. The primary outcome measure is self-reported hand activity performance at 3 months post-randomisation, as measured by the Functional Index for Hand Osteoarthritis (FIHOA); and a patient-generated measure of disability, the Patient-Specific Functional Scale (PSFS). Secondary outcome measures are self-reported OA symptoms (e.g. pain, stiffness and fatigue), the Patient Global Assessment of disease activity, measured hand function (e.g. grip strength, thumb web space and hand dexterity) and health-related quality of life. Cost-utility and cost-effectiveness analyses will be conducted.

**Discussion:**

This study will contribute to the knowledge on both the effect and resource use of an exercise programme with telephone follow-up on self-reported hand activity performance among people with hand OA.

**Trial registration:**

The trial is registered at ClinicalTrials.gov with registration number: NCT01245842.

## Background

Hand osteoarthritis (OA) is a common joint disorder that may lead to considerable pain and have a substantial impact on hand function [1]. The consequences of hand OA are of great importance, at the individual level in the form of suffering, reduced function and work ability; and at the societal level in the form of cost for health care and social security. Research on the Framingham Offspring and Community cohorts among women and men aged 28–92 years showed that the prevalence of radiographic hand OA was 51% for women and 48% for men, but that the prevalence of symptomatic hand OA (both radiographic changes and patient-reported symptoms) was 16% and 8% for women and men, respectively [2].

Hand OA may lead to pain both in and around affected joints, and a reduction in joint mobility and grip force, which in turn may result in activity limitations and participation restrictions [1,3]. The clinical manifestations are represented by soft tissue swelling, bony enlargements and bone erosions. These findings occur most frequently in the distal interphalangeal (DIP) and proximal interphalangeal (PIP) joints of the 2nd-5th fingers, as well as in the carpometacarpal (CMC1) joint of the thumb. Previous research indicates that levels of pain and disability are significantly higher among patients with CMC1 involvement, compared to those without CMC1 symptoms [4,5].

At present, no OA disease-modifying interventions are available; therefore, the pharmacological treatment of hand OA is primarily aimed at alleviating symptoms and preventing inactivity and functional loss. International recommendations for OA treatment and standards of care have been developed to improve hand OA management [6,7]. Non-pharmacological approaches are considered to be the core treatment for OA patients [8]; treatment recommendations for individuals with hand OA including functional assessments and instructions in joint protection and work techniques, together with an exercise regimen, thermal modalities and the use of assistive devices, braces or joint supports [6,7].

Although there is a considerable amount of research demonstrating the positive effects of exercise on pain and function in knee OA [9,10], and also partly in hip OA [10,11], research on the effects of exercises in people with hand OA is very limited [12]. Among the few clinical trials that have been done, some have evaluated the effect of exercise in addition to instructions in joint protection and splints [13-15]; whereas four studies have assessed the effect of exercise (including yoga exercises) alone [16-19]. However, in a recent systematic review [12] these studies were rated as having a “high risk of bias” due to methodological limitations such as non-randomisation allocation procedures or small sample sizes. Furthermore, some of the studies reported a positive effect of exercises (and splints) on pain, function or stiffness, while others found no significant effect. Hence, there is conflicting and very limited evidence for the effect of exercises on hand OA, and more and better studies are needed [12,20]. This paper outlines the protocol for an exercise trial with telephone follow-up for people with hand OA.

### Study objective

A randomised controlled trial (RCT) has been designed to investigate the effects of a 12-week exercise programme with telephone follow-up on self-reported hand activity performance among people with hand OA. Our hypothesis is that the intervention group will report better hand activity performance at the 3-month follow-up compared to the control group.

## Methods

### Study development

The study has been designed by a group of researchers with a background as occupational therapists or physiotherapists, and with experience in treating patients with hand OA and in performing clinical trials. Two patient research partners and three primary health-care professionals have also been actively involved in this process.

### Study design

The study has been designed as a pragmatic, assessor-blinded, parallel-group RCT to assess the superiority of a 12-week exercise programme, including telephone follow-up versus usual care at the 3-month follow-up. Measurements are collected at baseline, and at 3- and 6 months post-randomisation. The protocol adheres to the SPIRIT 2013 Statement, which defines standard protocol items for clinical trials [21], and the CONSORT guidelines for non-pharmacological interventions [22,23]. The study is designed to conform to the principles of the Declaration of Helsinki.

### Setting

The study is being conducted in two different Norwegian settings, in the Ullensaker primary health-care services and at Diakonhjemmet Hospital, Oslo. One occupational therapist in Ullensaker and one at Diakonhjemmet Hospital are leading the group exercises at the two locations, and an occupational therapist ([name]) at Diakonhjemmet Hospital is performing the telephone follow-up. Physiotherapists and occupational therapists in Ullensaker primary health care and at Diakonhjemmet Hospital are conducting the assessments.

### Participants

We aim to recruit 150 persons with hand OA from two different OA cohorts:

1) The Musculoskeletal pain in Ullensaker STudy – Osteoarthritis cohort (MUST OA), a cohort of persons with OA in their hands, hips and/or knees derived from a population-based postal survey sent to all inhabitants between 40 to 79 years of age (n = 12,370) in Ullensaker Municipality in 2010-2011[24]. Approximately 60% of the individuals with self-reported hand, hip or knee OA have attended a comprehensive clinical examination at Diakonhjemmet Hospital.

2) The Oslo Hand OA cohort, which is a cohort of Diakonhjemmet Hospital patients between the ages of 60 and 80 years enrolled between 2000 and 2002 [25].

Among these, persons with hand OA in accordance with the inclusion and exclusion criteria (Table 1) are being recruited to this RCT, and the recruitment process is outlined in Figure 1. Participant eligibility is checked by the principal investigator (NØ), using the clinical examination data for the MUST OA cohort, and by telephone screening among the Oslo Hand OA cohort. Eligible persons receive written information and a request to participate in the RCT, and baseline measurements are taking place on a regular schedule, with 12–18 participants each time.

**Table 1 T1:** Criteria of inclusion and exclusion

**Inclusion criteria**	**Exclusion criteria**
• Persons with hand OA according to the ACR classification criteria for clinical OA [26]:	• Persons with a cognitive dysfunction;
◦ Pain, aching or stiffness in the hand and 3 of the following:	• Persons who do not understand the Norwegian language;
◦ Hard tissue enlargement involving at least 2 of 10 selected joints	• Persons with inflammatory rheumatic diseases (e.g. rheumatoid arthritis, ankylosing spondylitis) or cancer;
◦ Hard tissue enlargement of at least 2 DIP joints.	• Persons who have recently experienced severe trauma;
◦ Less than 3 swollen MCP joints	• Persons who have recently undergone OA surgery or other major surgery;
◦ Deformity of at least 1 of the 10 selected joints	• Persons who have received steroid injections in their hand joints during the previous two months.
OR uni-/bilateral OA in the CMC1 joint	
• FIHOA* total score ≥5	
• Access to a telephone	

*The functional index for hand osteoarthritis (FIHOA, range 0–30 (0 = best activity performance, 30 = poor activity performance).

**Figure 1 F1:**
[figure not shown]
Flow diagram of the study protocol.

### Randomisation and allocation concealment

The randomisation schedule was prepared by the study biostatistician using a computer-generated random numbers table, and randomisation is carried out through the use of random permuted blocks. To help conceal the randomisation, consecutively numbered and sealed opaque envelopes prepared by an independent staff member are used. The envelopes are opened in sequence after the participant has completed all the baseline measurements.

### Blinding

The outcome assessors are blind to group allocation, and are not involved in providing the interventions. The written participant information tells participants that they have an equal chance of being randomised to the intervention versus the control group, but does not provide any details of the actual exercise programme. Allocation is revealed to the three occupational therapists delivering the intervention (group exercises and telephone follow-up), but participants are requested not to disclose details about their group allocation with the outcome assessor. The success of outcome assessor blinding will be evaluated during one group follow-up assessment for the outcome assessors in Ullensaker and one at Diakonhjemmet Hospital by asking the assessors to guess the participants’ group allocation. The statistician who will perform the main statistical analyses will be blinded to group allocation during the analyses.

### Training of research occupational therapists and physiotherapists

The occupational therapists delivering the intervention initially participated in a workshop together with three of the authors (NØ, IK, [name]) in order to agree on the principles of the exercise programme, and on the information and instructions that should be provided. The outcome assessors participated in a one-hour training session led by the principal investigator (NØ). During this training, the outcome assessors received instructions to screen every completed questionnaire for responder missing while the participant is still present.

### Intervention

Both the control and intervention groups receive “usual care”, which for most people in Norway with hand OA is limited to general practitioner visits (or infrequently, a referral to a consultation with occupational therapists in secondary care). During this study, the control group receives no particular attention, referral or treatment from the project group, and we expect that none, or only a few, will consult a health care professional for their hand OA. Only the intervention group receives the exercise intervention, including the telephone follow-up.

The exercise programme for people with hand OA was developed in 2010 based on the results from a systematic review of the design and effects of splints and exercise programmes, as well as from the American College of Sports Medicine (ACSM) recommendations for developing muscular strength and flexibility in older frail adults [12,27]. The development of the exercise programme followed the new Medical Research Council guidance [28] for developing and evaluating complex interventions, including pilot testing (manuscript under review). Exercises 1–3 aim to increase the muscular strength and stability of the shoulder girdle/upper arm muscles, as this may influence hand activity performance. Exercises 4–5 intend to maintain or increase the flexibility of the MCP, PIP and DIP joints, while exercise 6 aims to strengthen the mm. extensors and abductors pollicis. The purpose is to maintain the thumb web space, increase thumb stability and counteract the strong pull from the adductor pollicis muscle combined with increasing the weakness of the opposing thenar intrinsic musculature, which can be seen in individuals with CMC1 OA, thereby leading to thumb adduction deformity. Exercise 7 intends to increase grip strength. Pipe insulation tubes were chosen instead of balls or other round objects since the tubes allow for squeezing without involving the thumb adductor muscles, which may contribute to a thumb adduction deformity. For the same reason, there is no exercise included to increase the maximum opposition of the thumb (touch the base of the little finger with the thumb tip) or to strengthen the pinch or key grip, as such exercises may accelerate an evolving CMC1-deformity.

The programme starts with a warm-up period consisting of a few minutes of rubbing the hands together and doing arm swings. Exercises 1 – 7 are performed with 10 repetitions for the first two weeks and 15 repetitions for weeks 3 – 12 (Table 2). Thera Bands with different resistance are provided to the participants and tested to identify the Thera Band with an appropriate, individualised resistance. The rubber band is wrapped around the hands or around something else if the hand joints are painful. The participants are instructed to apply a moderate to vigorous intensity in the strengthening exercises and to gradually progress by adjusting the resistance (e.g. by shortening the length of the Thera Bands or changing to a different Thera Band with more resistance).

**Table 2 T2:** Exercise programme for people with hand osteoarthritis

**No.**	**Exercise illustration***	**Instructions**
1.		**Shoulder extension:** Sit on an armless chair, knees slightly flexed, and heels on the floor. Start position: hands partly pronated (thumb up), close to the knees. Pull the exercise band back, as the hands follow the thigh to the iliac crest.
2.		**Biceps curl:** Stand with the feet shoulder width apart, arms hanging down. Hands are supinated (thumb laterally). Bend both elbows, pulling the exercise band towards the shoulders.
3.		**Shoulder flexion:** Stand with the feet shoulder width apart, arms hanging down. Hands are pronated (thumb medially). Keep the elbows extended and lift the arms to face level.
4.		**Make an “O-sign”:** Keep the thumb IP and MCP joints slightly flexed throughout. First, open the hand as if grabbing a bottle. Bring the index finger tip to the thumb tip, keeping the MCP, PIP and DIP joints flexed. Open the hand again (“grab the bottle”). Repeat with the 3rd, 4th and 5th fingers.
5.		**Roll into a fist:** First, flex the 2nd to 5th DIPs and PIPs only (keep the MCPs extended). Then flex the MCPs. Hold for 5 seconds. Reverse: extend the MCPs only, then the PIPs and DIPs.
6.		**Thumb abduction/extension:** Put one or more small elastic band(s) around the 1st to 5th proximal phalanges. Rest the loose fist, pronated, on a flat surface. Keep the thumb MCP and IP joints flexed and abduct/extend the thumb. Hold for 5 seconds.
7.		**Grip strength:** Squeeze a pipe insulation tube as hard as possible (isometric hold) for 10 seconds.
8.		**Finger stretch:** Lay the right hand on a flat surface. Use the left hand to apply firm pressure for 30 seconds stretching the 2nd to 5th PIP and DIP joints. Repeat 2 times for each hand.
		If the finger joints are painful: stretch one finger at a time; place the 2nd to 4th finger tips (opposite hand) between the finger joints of the 2nd finger; press for 30 seconds.

*The person on the images has consented for the images to be published.

The intervention group attends one group session per week and does two home sessions per week in weeks 1–3. During weeks 4–7 and 9–12 they do three sessions per week on their own. There is a “booster” group session in week 8 to ensure adherence and to individually adjust the exercises. The group sessions last approximately 45 minutes, and are conducted in the afternoon in the locations of the Ullensaker Primary Health Care and at Diakonhjemmet Hospital. SMS reminders are sent one day in advance, and the intervention group additionally receives a weekly telephone call in the weeks without group sessions (weeks 4–7 and 9–12) for individualised advice that addresses the exercises and encourages programme adherence.

The intervention group keeps the exercise equipment after the intervention period and decides themselves if they want to continue performing the exercise programme. Moreover, no advice is given to the control group at this time, but after the 6-month follow-up, the control group is provided with exercise equipment and instructions in the exercise programme. The Ullensaker cohort will most likely be naïve to hand exercises, while some of the Oslo Hand OA cohort may have received instructions at Diakonhjemmet Hospital Outpatient Clinic in 2007/2008. The Oslo Hand OA cohort control group participants will be asked whether they have received instructions in hand exercises before. At the two follow-ups all participants in the control group will be asked whether they have performed hand exercises in the past 3 months.

#### Telephone follow-up

The complex process of changing one’s own behaviour demands both energy and active involvement, and proceeding as usual often means following the line of least resistance. Thus, individuals need motivating factors and support to continue exercising or to establish the habit of regular exercise [29,30]. Changing health behaviour with education and advice are positive ways of enabling persons to exercise regularly, and there is some evidence which suggests that monthly telephone contact may help improve the clinical status of people with OA [31]. Adherence to the intervention will be targeted during the telephone follow-up using Motivational Interview techniques, a client-centred information and motivation strategy based on cognitive behavioural theory and the trans-theoretical model [32,33]. It is designed to engage ambivalent or resistant clients in the process of health behaviour change, and provides health practitioners with a means of tailoring their interventions to suit the patient’s degree of readiness for change.

### Outcome measures

The outcome measures have been selected based on those recommended for clinical trials in patients with hand OA [34,35], and consist of a combination of patient self-reported outcomes and performance tests. All outcome measures are collected at baseline, 3 months (post-intervention, primary endpoint) and 6 months (Tables 3 and 4). If a participant is unable to attend the assessment on the given date (i.e. due to vacation, sickness, etc.), a new appointment is made. For extraordinary situations (i.e. long-term vacation), the questionnaire is sent by mail/e-mail or the most important outcome measures (marked in Table 3) are collected in a telephone interview.

**Table 3 T3:** Primary and secondary outcomes

**Primary outcome measures:**	**Measurement scale**	**Time***
Hand activity performance (The Functional Index for Hand OsteoArthritis, FIHOA [36]) #	0-30	0, 3, 6
Patient-generated disability (Patient-Specific Function Scale, PSFS [37]) #	0-10	0, 3, 6

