# Items included in the telephone interview when attendance is impossible.

**Table 4 T4:** Tertiary outcome measures

**Tertiary outcome measures**	**Measurement scale**	**Time***
Hand pain in which hand	Left/Right/Both	0, 3, 6
Which hand is most painful	Left/Right	0, 3, 6
Hand injury, surgery or injections over past three months	Single question	3, 6
Fatigue	Numeric rating scale (NRS): 0-10	0, 3, 6
Mental distress (General Health Questionnaire, GHQ-20 [40])	Bi-modal fashion (0-0-1-1)	0 months
Self-reported work ability [41]	5-point scale	0, 3, 6
Physical activity (International Physical Activity Questionnaire-Short Form, IPAQ [42])	Mean minutes/week, MET-minutes/week	0, 3, 6
• Vigorous-intensity activity		
• Moderate-intensity activity		
• Walking		
• Sitting		
Exercise self-efficacy [43]	7-point scale	0, 3, 6
Exercise diary (intervention group only)	dd.mm.yy	0-3
• Date	Minutes	
• Exercise duration	NRS: 0–10	
• Pain level post-exercise	Text	
• Comments	Kilogrammes	
• Grip strength at group sessions (weeks 2, 3 and 8)		
Adverse events (intervention group only, obtained from the exercise diary + telephone follow-up log)	Type, duration	0-3

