### Statistical analyses

#### Data analysis

Demographic and clinical characteristics as well as other baseline data are being collected and will be presented to assess the baseline comparability of the two groups. These variables will also be compared for those participants who withdraw from the study and those who remain. Parametric and non-parametric statistical analysis models will be used depending on the distribution of the variables.

The intention-to-treat principle (ITT) will be followed in the primary analyses of data, and will include all participants, also those who have missing data and those who are not fully compliant with the protocol. Descriptive statistics will be presented for each group as the mean change (standard deviation, 95% confidence intervals) in the outcomes from baseline to each time point. Differences in mean change from baseline to each time point will be compared between groups, using linear mixed models or generalised linear regression modeling, adjusting for baseline levels of the outcome measure. Model assumptions will be checked by standard diagnostic plots, and improvements in the intervention and control group based on the perceived ratings of change will be compared using logistic regression, and presented as odds ratios with 95% confidence intervals. Additionally, the number of “responders” in the two groups will be compared using the OMERACT-OARSI responder criteria [54]. A participant will be classified as a responder if one of the following is fulfilled:

1) High improvement:

•≥50% improvement + absolute change of ≥2 in self-reported hand pain (NRS, 0–10), OR

•≥50% improvement + absolute change of ≥6 in self-reported hand activity performance (FIHOA, 0–30);

OR

2) Improvement in at least 2 of the 3 following:

•≥20% improvement + absolute change ≥1 in self-reported hand pain

•≥20% improvement + absolute change ≥1 in Patient Global Assessment of disease activity (NRS, 0–10)

•≥20% improvement + absolute change ≥6 in self-reported hand activity performance (FIHOA)

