Some attrition is anticipated despite the fact that we have planned procedures to minimize loss due to follow-up and participant withdrawal, and to maximize adherence. This may represent a limitation insofar as the planned trial does not include a placebo or attention control intervention for the control group. However, no optimal solution for the content or delivery of a “sham exercise intervention” was identified and an educational intervention for the control group might have resulted in limited contrasts between the two groups. Hence, this study is designed as a pragmatic trial comparing the active intervention with the usual care.

In conclusion, this study will contribute to the knowledge of the effect of exercises with telephone follow-up on self-reported hand activity performance in people with hand OA, in addition to the cost-utility and cost-effectiveness of the exercise intervention.

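### The trigger for remote outcome collection is worded in two ways, and neither covers a consenting participant who declines the visit after rebooking

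*Protocol article*

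**What the plan says.** The Outcome measures section fixes the schedule without any condition on adherence: "All outcome measures are collected at baseline, 3 months (post-intervention, primary endpoint) and 6 months". It then gives two steps for a missed visit. The first is rebooking: "If a participant is unable to attend the assessment on the given date (i.e. due to vacation, sickness, etc.), a new appointment is made". The second is remote collection, under a condition that begins "For extraordinary situations (i.e. long-term vacation": the questionnaire goes by mail or e-mail, or the outcomes marked in Table 3 are taken by telephone interview.

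The Table 3 footnote describes the same telephone set with another trigger: "Items included in the telephone interview when attendance is impossible". The items marked # are FIHOA, PSFS, hand pain, hand stiffness and the four patient global ratings. Grip strength, dexterity, thumb web space and 15D are not marked.

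Under Data analysis, the intention-to-treat analysis "will include all participants, also those who have missing data and those who are not fully compliant with the protocol". The Discussion expects some attrition but adds that "we have planned procedures to minimize loss due to follow-up and participant withdrawal, and to maximize adherence". It does not describe those procedures.

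**The concern.** The stated triggers suit absences that probably have little to do with outcome, such as a long holiday. A participant who could come but chooses not to is in neither trigger. That choice may well be related to outcome: the exercises hurt or did not help, or a control participant sees little reason to travel.

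The arms also differ in contact. The exercise arm has four group sessions, SMS reminders and eight weekly calls. The control arm receives usual care with no particular attention from the project. Participants know their allocation, so reasons for declining a visit can differ by arm.

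At stake are the primary outcomes at 3 months. A participant who gives no follow-up data contributes only a baseline value. A baseline-adjusted model must then assume that the unseen outcome resembles that of attenders with a similar baseline. The planned comparison of baseline characteristics between those who withdraw and those who remain cannot test this. Collecting the data would remove the need for the assumption.

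**Working it through.** **1. Do the two triggers agree, and whom do they cover?**

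| Situation | Outcome measures text | Table 3 footnote |
|---|---|---|
| Missed date, can come later | Rebooked | Not addressed |
| Away for a long period | Remote collection | Remote collection (attendance impossible) |
| Cannot attend for another reason | Remote only if judged extraordinary | Remote collection (attendance impossible) |
| Could attend, declines after rebooking, still consents to data collection | No stated route | No stated route |
| Stopped exercising, attends | Normal visit | Not needed |

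The third row shows that the triggers differ. The fourth is the gap. The last shows that stopping exercise alone does not create it.

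**2. The plan's own figures.** The Sample size section gives a difference of 3 FIHOA points, SD 6.2, two-sided 5% and 80% power.

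- n per group = 2 × (1.960 + 0.842)² × 6.2² / 3² = 67.05, rounded up to 68 (the t-test version gives 68.02). The stated 68 reproduces.
- Drop-out of 10%: 68 × 1.10 = 74.8, so 75 as stated; 68 / 0.90 = 75.6, so 76 by the usual formula. The difference is immaterial here.
- With 75 randomised per group, power is 80.3% at 10% loss, 78.0% at 15% and 75.5% at 20%.

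**3. Illustration of bias.** Let d be the proportion of an arm that is missing. Let g be how much worse, in FIHOA points, the missing do than attenders with the same baseline. The full-arm mean is (1 − d) × attenders + d × non-attenders, so attenders look better than the full arm by d × g. The bias in the contrast is

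bias = d(exercise) × g(exercise) − d(control) × g(control).

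The article gives no g and no rate of declined visits. The values below are assumptions, with the second term set to zero (control losses uninformative).

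| d (exercise) | g = 1 | g = 3 | g = 6 |
|---|---|---|---|
| 10% | 0.1 | 0.3 | 0.6 |
| 20% | 0.2 | 0.6 | 1.2 |

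At 10% missing and g of 3 to 6, the bias is 0.3 / 3 = 10% to 0.6 / 3 = 20% of the 3-point difference. If both arms had the same d and g, the two terms would cancel: 0.10 × 3 − 0.10 × 3 = 0.

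**4. Effect on the test.** With 68 completers per arm, the standard error is 6.2 × √(2/68) = 1.06. If there were no true effect, a shift of 0.3 (0.28 standard errors) or 0.6 (0.56 standard errors) would raise the two-sided 5% error rate to about 6% or 9%.

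**The case against.** The strongest reply is that this is a condensed article. Details of retention contacts usually sit in the full protocol, and the Discussion says that procedures to limit loss and withdrawal are planned. The authors also seem to use i.e. to mean for example: the rebooking sentence ends its own i.e. list with etc., and the 15D description lists four of fifteen dimensions after i.e. So a long vacation is best read as an illustration, and a site might well telephone a decliner.

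That reply defeats two stronger readings. A reader might infer that participants who stop exercising are denied follow-up. The documents do not support this: the schedule has no adherence condition, and non-compliant participants are kept in the analysis. A reader might also infer that decliners' outcomes are certain to be lost. The article is silent on decliners. It does not exclude them, so loss is a risk and not a stated fact.

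The reply leaves the narrower point standing. The article does state a trigger, in two places and in two forms. Even with i.e. read loosely, extraordinary and impossible do not describe a visit that was simply declined.

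Two further points against also have force. The 10% is a general drop-out allowance, which can include withdrawn consent and illness that a wider trigger would not recover. And keeping remote collection behind rebooking is sensible, because the performance tests need a visit.

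**Conclusion.** The concern holds in limited form. The two triggers for remote collection differ and should be reconciled. Neither gives a route for a randomised participant who still consents to data collection but declines the visit after rebooking. No measurement reason is given for the limit, since both primary outcomes are self-reported and already in the telephone set.

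The size cannot be derived from the document. The 0.3 to 0.6 points is an illustration that treats every exercise-arm loss at 10% as informative and every control loss as uninformative. It is not the bias that rewording would remove. Losses alike in both arms would shrink or cancel it. The case for change rests on the low cost of collecting outcomes that the analysis cannot otherwise recover, in a trial with unequal contact between arms.

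**What to change.** Use one rule in both the Outcome measures section and the Table 3 footnote. After rebooking has been tried, seek the questionnaire by mail or e-mail, or the # items by telephone, at 3 and 6 months. This applies to every randomised participant who has not attended and has not withdrawn consent to data collection, whatever the reason and whether or not they still exercise. Say that stopping the exercises is not withdrawal from follow-up. Have an existing blinded assessor make the call, and record the mode and the reason for non-attendance by arm.

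The cost is a reworded rule, a few short calls and a small addition to the data form. Some outcomes will come by a different mode, which the article already accepts. These participants will have no performance tests, and no 15D if only the telephone is used. PSFS is described as interview-administered, so the telephone is the remote route that clearly covers both primary outcomes. Keeping rebooking as the first step limits the number who move from a visit to a call.
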